##### 7. Qualitative work: ease of administration and GP feedback

Running an IME is not trivial and a method that provides some administrative benefits (*e.g*., easier to put scenarios together, easier to pilot scenarios with some participants, easier to change the order of scenarios, easier to deliver to participants, easier to manage collected data) has efficiency advantages. We will compare, via interviews, experiences of the research team with running paper-based and web-based IMEs. This will, of course, be subjective (although item four will provide some quantitative information about effort linked to recruitment) but will nevertheless provide useful information about the effort required by researchers to run an IME via each approach. Here, we are looking for the method that is considered easiest to use and which uses fewest resources for an IME.

We will also consider qualitative feedback from GPs on the web-based delivery method and the utility of decision time data collected in the web-based IME, which is impossible to measure with paper-based IMEs. This work will also consider how the differing configurations of the interventions might explain their effects. Here, we are looking for feedback from GPs that identifies whether they think web-based IMEs have face validity, that the approach is feasible, and that they would participate in future web-based IMEs.

For the email versus postal invitation trial, the primary outcome is the number of GPs completing the first questionnaire. There are no secondary outcomes.

### Safety

No safety issues or potential adverse events linked to participation are envisaged.

### Statistics

#### Sample size

Our sample size will be 250 GPs completing the first questionnaire, 75% of whom will be invited to complete the second questionnaire. GPs who are already likely to be following best evidence with regard to prescribing antibiotics will be excluded from the second questionnaire, which we will do by excluding those in the first quartile of 'intention to prescribe' responses to the first questionnaire. These 25% of GPs will be thanked but will not continue in the study. For the first questionnaire analysis, our required sample size will be 162 based on a recommendation by Green [23] for multiple regression analysis with 14 predictor variables. The analysis of the questionnaire data will check the internal consistency of the measures and use multiple regression analysis to examine the relationships between predictor and outcome variables.

Using the dependent variable of behavioural intention, we will seek to detect an effect size of 0.66. This was the mean effect size for change in intention in a meta-analysis of trials that measured change in intention and behaviour [24]. This 'medium to large' change in intention led to a 'small to medium' change in behaviour. We will require 50 participants per group to have 90% power of detecting this effect size at a significance level of 5% to 150 participants in total. We anticipate having 187 GPs in our 75% sample from the first questionnaire study, which will allow for some dropout.

The effect of each intervention will be estimated by comparing the change in intention in each of the active intervention groups with that in the control group. This procedure will be repeated with behavioural simulation as the dependent variable. We propose to take the intervention with the largest effect size forward into a definitive trial; there is a risk of wrongly choosing this as the most effective (a type 3 error). With 50 practitioners per group if treatment B is actually superior to treatment A, such that the standardised difference in mean scores is 0.38, the probability of incorrectly choosing treatment A is 5%.

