## Methods

### Trial design

#### General

The study will include two trials, one a web-based IME, the other an evaluation of the method used to invite GPs to take part in the web-based IME. The basic design of these two trials will be:

1. Web-based IME: a three-arm, double-blind, randomised controlled trial of two behaviour change interventions compared to generic information.

2. Invitation: a two-arm, randomised controlled trial of an email invitation to GPs compared to a postal invitation.

The web-based IME will be based on a previous paper-based IME [6]. This earlier work provided qualitative data about the kind of attitudes and beliefs among GPs about the use of antibiotics in the treatment of URTIs (cough/cold, sore throat/tonsillitis in patients of any age). This was used to develop questionnaire items relevant to the clinical context of treating URTIs in primary care and which operationalised the constructs of our chosen theories (*e.g*., theory of planned behaviour: questionnaire has an item asking GPs whether they thought patients expected them to prescribe an antibiotic, which is linked to the theory's subjective norms construct). The earlier work also developed clinical scenarios describing patients presenting in primary care with symptoms of URTI. GPs were asked to report their clinical decisions in response to the scenarios and these were used to generate scores for 'simulated behaviour.' We will use a web-based IME to deliver the questionnaire and scenarios to GPs in order to identify predictors of prescribing behaviour and compare these with those identified in the paper-based IME.

The research study is based in the Division for Clinical and Population Sciences and Education at the University of Dundee at Ninewells Hospital, with support from the Universities of Aberdeen, Newcastle and Southampton and the Scottish School of Primary Care. It is funded by the Chief Scientist Office, grant number CZH/4/610 and approved by the Tayside Committee on Medical Research Ethics A, REC reference 10/S1401/54. A flow diagram of the study is shown in Figure 1.

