#### Randomisation

The study statistician will generate a list of random numbers to be used by SPCRN to randomly allocate GPs to receive either an email or postal invitation on a 1:1 basis. There will be no stratification. The list will be generated using Stata 11.0 statistical software (StataCorp, College Station TX). To ensure we do not approach too many GPs to participate in the main study we will randomise two initial blocks of 250 GPs (see Sample size) then subsequent blocks of 50 GPs will be contacted until the required sample size for the web-based IME is met.

All GPs will complete the same, initial web-based questionnaire to identify predictors of behavioural intention and simulated behaviour. GPs will receive one of two interventions (one of which will be a persuasive communication) or a comparator with the second web-based questionnaire. The study statistician will generate a list of random numbers for allocation to intervention or comparator on a 1:1:1 basis, which will be loaded into the web-based IME system. Allocation will, therefore, be done by the system when the GP logs onto the web-based IME system to complete the second questionnaire. There will be no stratification.

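### The 5% wrong-selection risk does not match the stated choice between two interventions: with 50 per group and a 0.38 SD difference it is 2.9% (a minor, conservative error)

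*Protocol article*

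**What the plan says.** The web-based experiment is "a three-arm, double-blind, randomised controlled trial of two behaviour change interventions compared to generic information" (Methods, General), with "allocation to intervention or comparator on a 1:1:1 basis" (Randomisation). Under Statistics, Sample size, the effect of each intervention is to be estimated by "comparing the change in intention in each of the active intervention groups with that in the control group". The rule for what happens next is: "We propose to take the intervention with the largest effect size forward into a definitive trial".

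The protocol acknowledges that this rule can pick the wrong intervention, calls that a type 3 error, and quantifies it for 50 GPs in each arm with B the truly better intervention: "such that the standardised difference in mean scores is 0.38, the probability of incorrectly choosing treatment A is 5" per cent. It gives no formula. It does not say whether the selection is modelled as between two interventions or among three arms, nor on which standard deviation the 0.38 is scaled.

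**The concern.** The sentence supplies everything needed to check it: a group size, a true standardised difference, two named treatments and a rule that takes the larger effect. When those inputs are put together, the result is not 5%.

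This is the only operating characteristic that the article gives for choosing which intervention goes on to a definitive trial. A reader who relies on it would think that the design needs a difference of 0.38 SD to hold the risk of a wrong choice at 5%. A reader who tries to reproduce it from the stated design cannot.

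**Working it through.** **Inputs** (protocol article, Sample size, unless noted)

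- Group size n = 50.
- True difference, B better than A: d = 0.38 SD.
- Stated probability of choosing A: 5%.
- Rule: the intervention with the larger observed effect is taken forward, with no significance test.
- Three arms, two of them interventions (General); equal allocation (Randomisation).

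**1. The choice as worded: A or B.** Both effects are measured against the same control group, so the control mean cancels and A is chosen when its mean effect exceeds B's.

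- Standard error of the difference in standardised means: sqrt(2/50) = 0.20.
- P(choose A) = Phi(-0.38/0.20) = Phi(-1.90) = 2.9%.
- Rounding of 0.38: 0.375 gives 3.0% and 0.385 gives 2.7%. A t reference with 98 degrees of freedom gives 3.0%. None of these reaches 5%.
- Difference that gives 5% at 50 per group: 1.645 x 0.20 = 0.33 SD.

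**2. Which calculation reproduces the stated 5%?**

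| Model, n = 50 per group, d = 0.38 | Probability |
|---|---|
| A versus B, shared control | 2.9% |
| The same, doubled as if two-sided | 5.7% |
| A versus B, as if each had its own control group | 9.0% |
| Best of three equal groups, both others 0.38 SD below the best: best not selected | 5.2% |

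The last row is 1 - BVN(1.90, 1.90; correlation 0.5), where BVN is the bivariate normal distribution function. Solving it for exactly 5% gives 0.383 SD, which rounds to the stated 0.38. This is the closest match at the stated group size.

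**3. Does the three-group model make the sentence true?** In a simulation of four million draws under that model, B was chosen 94.8% of the time, A 2.6% and the third group 2.6%. So even there the probability of choosing A is about half the stated figure. The model also needs the control to equal A, that is, an intervention A with no effect. If the control is instead 0.66 SD below B (the effect size used for the main calculation) with A still 0.38 SD below B, the total probability of not selecting B is again 2.9%.

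**4. Scale.** Suppose 0.38 refers to the SD of raw scores. The correlation r between baseline and follow-up then matters. The article does not give it, so a range is shown as an assumption.

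| Assumed r | Change scores | ANCOVA |
|---|---|---|
| 0.3 | 5.4% | 2.3% |
| 0.33 | 5.0% | 2.2% |
| 0.5 | 2.9% | 1.4% |
| 0.7 | 0.7% | 0.4% |

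The formulas are Phi(-0.38/(0.20 x sqrt(2(1 - r)))) for change scores and Phi(-0.38/(0.20 x sqrt(1 - r^2))) for ANCOVA.

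**5. Main sample size.** The plan states: "We will require 50 participants per group to have 90% power of detecting this effect size at a significance level of 5" per cent. Check for 0.66 SD, two-sided: n = 2 x (1.960 + 1.282)^2 / 0.66^2 = 48.2, so 49 per group. At 50 per group the power is Phi(0.66/0.20 - 1.96) = Phi(1.34) = 91%, or about 90% by t-test. This calculation is sound.

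**The case against.** The strongest defence is that the number is not a slip at all. Selection of the best of three equal groups is a standard problem, the trial has three equally allocated arms, and at 50 per group the 0.38 and the 5% belong together under that model. On this view the figure is right and only its description is loose. The numerical match is a good reason not to call the figure a plain miscalculation. It does not rescue the sentence, which names A and B only and gives the probability of choosing A. The generic-information comparator is not an intervention that could be taken forward. The three-group origin also remains an inference, since the article shows no formula.

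A second defence is that the scale is unstated. With raw-score SDs and a comparison of change scores, 5% does arise at a correlation near 0.33. The Sample size section does speak of change in intention, so the scale should be named. But the Statistical analysis section specifies ANCOVA for the primary outcomes, and under ANCOVA the risk is 2.9% or less at any correlation.

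A reader might also notice that, for a choice between two interventions, 0.38 SD and 5% go together at 2 x (1.645/0.38)^2 = 37.5 per group, which happens to equal 150 x 0.75 / 3. From this one might infer that the real group size is about 37 and that the power for 0.66 SD is overstated. The document does not support that. It applies the 75% to 250 GPs, anticipates 187 for the second questionnaire, and gives 150 as the number required after that cut. No section mentions 37 per group.

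**Conclusion.** The concern holds as a mismatch between a figure and its description. For the choice that the protocol describes, the probability of incorrectly choosing A at a true difference of 0.38 SD with 50 per group is 2.9%, which is 2.1 percentage points below the stated 5%. Put the other way, the 5% belongs to 0.33 SD. This assumes approximately normal mean scores, 0.38 expressed on the SD scale of the analysed outcome, and selection on the larger observed effect against a shared control.

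The point is minor. The error is conservative: the design is somewhat better at separating the two interventions than the protocol claims. It would be wrong to infer that the trial is too small or that the selection rule is riskier than stated. The group size rests on 0.66 SD and 90% power, which checks out, and neither the analysis nor the selection rule changes.

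**What to change.** Replace the sentence in the Sample size section with wording such as: *With 50 per group, if B is superior to A by 0.38 SD, the probability of incorrectly choosing A is 2.9% (5% at 0.33 SD)*, and state that the SD is that of the analysed outcome.

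If the 5% was meant as the probability of failing to select the best of three groups, say so and give the configuration (both other groups 0.38 SD below the best, 50 per group). Explain as well why the comparator counts as a candidate.

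The cost is one sentence. The group size and the power statement should stay as they are.

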### Statistical analysis

For the web-based IME trial, reporting will be in line with the CONSORT statement [25]. Data will be summarised by intervention group using appropriate descriptive statistics where required, for example, mean and standard deviation for the primary outcomes. The primary outcomes will be analysed using an analysis of covariance (ANCOVA) framework to correct for the baseline levels of intention and behavioural simulation. Effect sizes will presented with estimated 95% confidence intervals of the two new interventions versus generic information as the comparator. All analysis will be by intention to treat. Missing data at baseline are impossible by trial design, missing outcome data due to non-response to second questionnaire will not be imputed, analyses will be by responders only. Characteristics of responders and non-responders baseline data will be compared to assess the impact potential non-response on results. Secondary outcome will be analysed in a similar manner to the primary outcomes.

For the email versus postal invitation trial, reporting will also be in line with the CONSORT statement [25]. The primary outcome will be presented as the proportion of GPs sent an invitation completing the first questionnaire by invitation method. Proportions will be compared using a simple chi-square test, and results presented as an odds ratio and 95% confidence interval. There are no secondary analyses for this trial.

## Discussion

The National Health Service and other healthcare providers need effective quality improvement interventions to be put into clinical practice, which requires effective behaviour change interventions. IMEs are a way of exploring and refining an intervention before moving to a full-scale trial as recommended in the MRC framework for evaluating complex interventions. IMEs do this by delivering key elements of the intervention in a simulation that approximates clinical practice by, for example, presenting GPs with a clinical scenario about making a treatment decision. Earlier IMEs have been paper-based, which limits what can be done in the simulation.

Web-based IMEs provide the potential for better clinical simulations, which can be expected to lead to better interventions. The study described here will run a full, web-based IME involving 250 GPs that will advance the methodology of IMEs by directly comparing results with an earlier paper-based IME. Moreover, the web-based IME will evaluate an intervention that can be put into a full-scale trial that aims to reduce antibiotic prescribing in primary care. Reducing inappropriate prescribing of antibiotics in general practice is a national priority; indeed, antibiotic use is increasing in the UK and Scotland's prescribing is second highest amongst UK administrations. More effective behaviour change interventions are needed, and this proposal will develop one such intervention and a system to model and test future interventions. This system will be applicable to any situation in a healthcare system where behaviour needs to be modified, including interventions aimed directly at the public.

We believe the web-based IME system will reduce the overall cost of trials by requiring fewer iterations of full-scale trial/analysis/revisions/full-scale trial before an optimised intervention is produced, thereby making better use of limited research budgets for trials. Finally, a web-based system can involve a wide range of stakeholders, expanding the range of opinions that can feed into intervention design and development, and enhancing the implementation potential of quality improvement initiatives.
